**Table 1: Hormonal Assessment (acceptable timeframe of previous blood draws)**

| Measurement                                                                                                   | Mandatory                | Optional | Timeframe                                                                                                                                                                                                                                                                                                                                                                                                                                                                             |
|---------------------------------------------------------------------------------------------------------------|--------------------------|----------|---------------------------------------------------------------------------------------------------------------------------------------------------------------------------------------------------------------------------------------------------------------------------------------------------------------------------------------------------------------------------------------------------------------------------------------------------------------------------------------|
| Plasma
normetanephrines and
metanephrines
OR
urine
normetanephrines and
metanephrines       | Exclusion
Criterion 3 |          | If < ULN, measurement up to 12 months before screening will be accepted if the adrenal tumor has already been diagnosed at that time and measurement was done for hormonal evaluation of the respective adrenal tumor

If > ULN, measurement should be no older than 3 months before screening.                                                                                                                                                                                 |
| Plasma/Serum
Aldosterone
AND
Plasma renin concentration
OR
Plasma renin activity | Exclusion
Criterion 4 |          | If plasma/serum aldosterone concentration (ng/l) to plasma renin concentration (ng/l) ratio (or equivalent) < cutoff for the respective laboratory, measurement up to 12 months before screening will be accepted if the adrenal tumor has already been diagnosed at that time and measurement was done for hormonal evaluation of the respective adrenal tumor.

If ARR > cutoff for the respective laboratory, measurement should be no older than 3 months before screening. |

|                                                                                       |                         |                                                                                                                |                                                                                                                                                                                                                                                                                                                |
|---------------------------------------------------------------------------------------|-------------------------|----------------------------------------------------------------------------------------------------------------|----------------------------------------------------------------------------------------------------------------------------------------------------------------------------------------------------------------------------------------------------------------------------------------------------------------|
| Dexa Suppression Test
(morning serum cortisol after 1 mg dexamethasone at 23.00 h) | (Exclusion Criterion 5) | One of the tests is mandatory (which one is at the discretion of the investigator). If the test performed does | If < 2.5 µg/dl, measurement up to 12 months before screening will be accepted if the adrenal tumor has already been diagnosed at that time and measurement was done for hormonal evaluation of the respective adrenal tumor.
If > 2.5 µg/dl, measurement should be no older than 3 months before screening. |
| Plasma ACTH                                                                           | (Exclusion Criterion 5) | not fulfill the exclusion                                                                                      | Not older than 3 months before screening.                                                                                                                                                                                                                                                                      |
| Urinary free cortisol
OR
bed time (23.00 h)
salivary cortisol         | (Exclusion Criterion 5) | criteria no further tests are necessary.                                                                       | Not older than 3 months if the adrenal tumor has already been diagnosed at that time and measurement was done for hormonal evaluation of the respective adrenal tumor.                                                                                                                                         |
| DHEAS
17-OH-Progesterone                                                           |                         | Optional                                                                                                       | Up to 12 months before screening if the adrenal tumor has already been diagnosed at that time and measurement was done for hormonal evaluation of the respective adrenal tumor.                                                                                                                                |

The documentation of the hormonal assessment is adapted from the ENS@T criteria: Study sites are highly encouraged to follow these.

## 7.2 Diagnostic Phase

Upon completion of all screening tests and confirmation of eligibility, patients will be included in the diagnostic phase of the study. Diagnostic evaluation (**Visit 2 and 3**) will start within four weeks after screening.

Patients will be evaluated by both [I]Iodometomidate SPECT/CT and [F]Fluorodeoxyglucose PET/CT (see standard operating procedures in the Appendix). Computed tomography will be performed as low dose CT of the adrenal region to reduce radiation exposure. Imaging can be started with either [I]Iodometomidate SPECT/CT or [F]Fluorodeoxyglucose and can be performed on two consecutive days. The time interval between [I]Iodometomidate SPECT/CT and [F]Fluorodeoxyglucose should not exceed 8 weeks if both imaging is done within the study.

If [ $^{18}\text{F}$ ]Fluorodeoxyglucose PET has already been performed prior to inclusion in the study only [ $^{123}\text{I}$ ]Iodometomidate SPECT/CT will be performed and [ $^{18}\text{F}$ ]Fluorodeoxyglucose PET results will be included in the final analysis if FDG-PET has been performed at maximum three months before study inclusion and if the PET was performed in accordance with usual standard of care.

After the completion of imaging, the patient will enter the follow-up phase.

### 7.3 Follow-up phase

Patients will have a follow up visit 2-4 weeks after [ $^{123}\text{I}$ ]Iodometomidate SPECT/CT and [ $^{18}\text{F}$ ]Fluorodeoxyglucose PET/CT - or immediately before surgery (within the preoperative routine will suffice), if surgery performed within 2 weeks post imaging. (**Visit 4**). Routine laboratory tests will be repeated:

Serum-creatinine, urea, glomerular filtration rate (MDRD), blood count, aspartate aminotransferase, alanin aminotransferase, alkaline phosphatase, and gamma glutamyl transferase.

Patients will further be interviewed regarding possible adverse events due to imaging.

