| 24 hour urine                                                          | X                |                           |                           |                                                                                    |                                                                                 |
| Follow up imaging CT or MRI of adrenal region e             |                  |                           |                           |                                                                                    | (X)                                                                             |
| [  F]Fluorodeoxyglucose PET/CT                            |                  | X (if not at visit 3)     | X (if not at visit 2)     |                                                                                    |                                                                                 |
| [  I]Iodometomidate SPECT/CT                             |                  | X (if not at visit 3)     | X (if not at visit 2)     |                                                                                    |                                                                                 |

- a Routine blood tests: Serum-creatinine, urea, glomerular filtration rate (MDRD), blood count (haemoglobin, leukocytes, platelets), aspartate aminotransferase, alanin aminotransferase, alkaline phosphatase, and gamma glutamyl transferase. If done within 2 weeks before V1, then no need to repeat.
- b Hormonal assessment: Morning serum cortisol after 1 mg dexamethasone 23:00, (urinary free cortisol), (midnight salivary cortisol), baseline plasma ACTH, plasma renin concentration or plasma renin activity, serum aldosterone, (DHEAS), (17-OH-progesterone) , plasma metanephrines/plasma normetanephrines or urinary metanephrine/normetanephrine excretion (*Table 1*)
- c At the discretion of investigator. This should follow usual care at the respective clinic of nuclear medicine, since pregnancy should be ruled out for almost all routine procedures: If in routine care this is only done by questioning then this should suffice.
- d AEs will be collected from inclusion of study to visit 4.
- e Only in case of refusal of surgery, follow up imaging (CT or MRI) will be performed 6-12 months after inclusion into the study and at the discretion of the attending physician

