### 7.6.2 Safety Assessments

All subjects will have a physical examination at screening.

Routine blood tests: Serum-creatinine, urea, glomerular filtration rate (MDRD), blood count (haemoglobin, leukocytes, platelets), aspartate aminotransferase, alanin aminotransferase, alkaline phosphatase, and gamma glutamyl transferase will be performed at Visit 1 and Visit 4 (2-4 weeks after imaging). Adverse events will be assessed at every study visit. NCI-CTCAE v.4 will be used to report toxicity

([https://evs.nci.nih.gov/ftp1/CTCAE/CTCAE\\_4.03/CTCAE\\_4.03\\_2010-06-14\\_QuickReference\\_5x7.pdf](https://evs.nci.nih.gov/ftp1/CTCAE/CTCAE_4.03/CTCAE_4.03_2010-06-14_QuickReference_5x7.pdf))

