## **8.6 Safety analysis**

Standard routine parameter changes from before imaging to prior to surgery will be assessed. Adverse events will be assessed from registration until end of follow up which is Visit 4. Surgery or biopsy of the adrenal lesion(s) is expected within the range of 1-6 weeks after the second imaging. Adverse and serious adverse events will be presented using standard descriptive statistical methods.

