## **9 ADVERSE EVENTS AND SERIOUS ADVERSE EVENTS**

### **9.1 Definition**

#### **9.1.1 Adverse Event (AE)**

An Adverse Event (AE) is any new untoward medical occurrence or worsening of a pre-existing medical condition in a patient or clinical investigation subject administered an investigational (medicinal) product. An AE can therefore be any unfavourable and unintended sign (including abnormal laboratory findings for example), symptom, or disease temporally associated with the use of a medical product, whether or not a causal relationship (i.e. related/not related) with the treatment is suspected.

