### 9.3.2 Adverse Event (AE) and Serious Adverse Event (SAE) Documentation and Reporting

All observed AE regardless of treatment group or suspected causal relationship to study drug will be assessed following NCI-CTCAE version 4.0 and recorded on the AE page of the CRF, and in the case of a serious adverse event will also be recorded on a SAE form.

All SAEs must be reported immediately (i.e., within 24 hours of the Investigator's knowledge of the event) by facsimile of the SAE Report Form to the Würzburg Study Centre (Endocrinological Trial Unit):

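### Section 7.3 limits the Visit 4 interview to adverse events due to imaging, against the all-cause recording rules in Table 2, 7.6.2, 9.3.1 and 9.3.2

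*Protocol*

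**What the plan says.** Section 7.3 sets out what happens at Visit 4. The timing is given by "Patients will have a follow up visit 2-4 weeks after" the two scans, or immediately before surgery if that falls within two weeks of imaging, when the preoperative work-up may serve as the visit. Routine laboratory tests are repeated. On adverse events the instruction is: "Patients will further be interviewed regarding possible adverse events due to imaging".

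The other sections set the scope more widely. Section 7.6.2 says: "Adverse events will be assessed at every study visit". Table 2 marks AE/SAE assessment at Visits 1 to 4, and its note d says: "AEs will be collected from inclusion of study to visit 4". Section 9.3.1 asks for any AE between consent and Visit 4 to be recorded. Section 9.1.1 defines an AE "whether or not a causal relationship (i.e. related/not related) with the treatment is suspected". Section 9.3.2 applies severity grading and CRF recording to "All observed AE regardless of treatment group or suspected causal relationship to study drug". Section 9.4 requires SAEs to be reported whether related or not. Causality is a separate step: section 9.3.4 has the investigator classify each event as related or not related.

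**The concern.** The protocol's own sequence is to record the event first and judge its cause second. The 7.3 sentence reverses this at Visit 4, because the patient is asked about events already attributed to imaging. Attribution then passes from the investigator, who has a defined rule in 9.3.4, to the patient or to whoever conducts the interview.

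Adverse events are a stated safety outcome in the synopsis. They feed the yearly toxicity listing to the Independent Data Monitoring Committee (11.2), and unexpected toxicity is a ground for considering early termination (3.3.3). The events most likely to be missed by a question framed around imaging are those nobody expects imaging to cause. Thyroid blocking is a smaller example: it continues for 1 to 3 days (6.2, 17.3.1), and a patient asked about imaging may or may not think to mention a reaction to it.

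**Working it through.** No sample size, power or event figure enters this point, so there is nothing to reproduce. The check sets the provisions side by side and then traces which contacts follow each tracer.

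**Step 1: scope of each rule**

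| Protocol section | What it governs | Limited by suspected cause? |
|---|---|---|
| 7.3 | Questions put to the patient at Visit 4 | Yes, to imaging |
| Table 2, AE/SAE row and note d | Collection at Visits 1 to 4 | No |
| 7.6.2 | Assessment at each visit | No |
| 9.1.1 | Definition of an AE | No |
| 9.3.1 | Recording from consent to Visit 4 | No |
| 9.3.2 | Grading and CRF entry | No |
| 9.4 | SAE reporting | No |

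Section 7.3 stands alone. It is also the section that describes the conduct of Visit 4.

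**Step 2: do the wider rules cure the narrow one?** Only in part. They require all-cause recording, so nothing permits a known event to be left out. But 9.3.2 applies to events that have been observed. For a symptom that resolved before Visit 4 and left no laboratory trace, observation depends largely on what the patient is asked. A narrow question can therefore shrink the set to which the wide rule applies.

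**Step 3: scheduled AE contacts after each tracer (section 7.2 and Table 2)**

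- Both scans done in the study: Visit 3 is an AE contact after the first tracer. After the second tracer, whichever it is, the next routine contact is Visit 4.
- FDG-PET done up to three months before inclusion, so that only IMTO is given in the study: after the IMTO visit, the only scheduled AE contact is Visit 4.
- Visit 5 does not fill the gap. It applies only if surgery is not performed, concerns follow-up imaging, and has no AE mark in Table 2.

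**Step 4: size.** An estimate of the loss would need the rate of AEs between the last scan and Visit 4, and the fraction that patients would not attribute to imaging. The protocol gives neither, so no figure is offered.

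**The case against.** The strongest reply is that 7.3 neither says that patients are asked about nothing else nor tells staff to leave other events out. Table 2, 7.6.2, 9.3.1 and 9.3.2 all apply at Visit 4 and already require what the fix asks for. The laboratory tests repeated at that visit are an independent route, since 9.3.2 gives criteria for reporting abnormal findings as AEs. Thyroid blocking is written into the IMTO procedure, so imaging can reasonably be read to include it. All of this stands, and it limits the point to contradictory wording that carries a risk. It does not remove the contradiction, and sites that follow the visit description in 7.3 literally have a text to rely on.

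A reader might infer two stronger claims, and the protocol supports neither.

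- *Visit 4 is the only AE contact after any tracer.* This is wrong when both scans are done in the study, because Visit 3 follows the first tracer.
- *The safety analysis pools events before and after tracer.* Section 8.6 says "Adverse events will be assessed from registration until end of follow up which is Visit 4" and "Adverse and serious adverse events will be presented using standard descriptive statistical methods", but does not say that the two periods are combined. Onset dates (9.3.5) and causality (9.3.4) are recorded, so the split is available, and table layout and denominators are commonly left to the SAP. The Table 2 maxima do give a window of 4 + 8 + 4 = 16 weeks, of which 12/16 = 75% precedes IMTO if it is scanned second. That is not time before any tracer: with both scans in the study, only 4/16 = 25% precedes the first. Nor would the two effects reinforce each other. Missed events after tracer lower the reported rate, while included events before tracer raise it.

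**Conclusion.** The point holds as a contradiction within the protocol: one visit description restricts the AE question by cause, while the recording rules do not. The consequence is a risk of incomplete elicitation after the second scan, and after IMTO for patients with an earlier FDG-PET. It is not a prescribed under-recording of events, and its size is unknown.

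The conclusion assumes that at least some sites will take the Visit 4 question from 7.3 as written. If every site works from 9.3.1 and 9.3.2, the practical effect is nil and the correction is one of consistency. The primary diagnostic analysis is untouched, and so is the rule in 9.4 on reporting SAEs. The matter is minor, but it belongs in the protocol, because an SAP cannot restore events that were never elicited. No change to 8.6 follows from it.

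**What to change.** In section 7.3, replace the limitation to imaging-related events so that patients at Visit 4 are asked about *any adverse event since the last visit, whatever the suspected cause*, and add that causality is then assessed under 9.3.4. This brings 7.3 into line with Table 2 note d, 7.6.2, 9.3.1 and 9.3.2.

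The cost is one sentence. The recording rules, causality classification and onset dates already exist. The downside is that a few more unrelated events will have to be recorded and classified at Visit 4.

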### 7.4 Study Duration

Study duration for each patient is the time from inclusion to **Visit 4** (Follow up).

In case of refusal of surgery, investigators are highly encouraged to follow the current guidelines on management of incidentalomas that suggest a follow up after 6 -12 months - including follow up imaging by either computed tomography or MRI (19). If imaging is performed – not as study procedure but at the discretion of the investigator – imaging data should be recorded in the CRF (**Visit 5**).

## 7.5 Subject discontinuation

The following events are considered as reasons for discontinuing a subject from the study:

- Adverse Event(s) with failure to recover
- Withdrawal of consent
- Pregnancy
- Death
- Protocol violation

The reason for discontinuation should be recorded in the CRF and in the source documents.

## 7.6 Table of Events or Visit Schedule and Assessments

Table 2 lists all of the assessments and indicates with “X” the visits when they are performed. All data obtained from these assessments must be supported in the patient’s source documentation.

### 7.6.1 Screening failure

Patients who complete the informed consent process and do not meet all entry criteria and therefore are not eligible for inclusion will be considered as screening failures. Patient’s characteristics such as age, gender and reason of screening failure will be described.

**Table 2: Visit Plan/Schedule of Assessments**

| Events                                                                 | Screening Period | Diagnostic Period         |                           | Follow-up Period                                                                   |                                                                                 |
|------------------------------------------------------------------------|------------------|---------------------------|---------------------------|------------------------------------------------------------------------------------|---------------------------------------------------------------------------------|
|                                                                        | Visit 1          | Visit 2                   | Visit 3                   | Visit 4                                                                            | (Visit 5 e )                                                         |
| Timepoint                                                       | Day 0     | ≤ 4 weeks after V1 | ≤ 8 weeks after V2 | 2-4 weeks after V3 or preoperative surgical routine – whichever comes first | 6-12 months after V3

Only in case that surgery is not performed |
| Informed Consent                                                       | X                |                           |                           |                                                                                    |                                                                                 |
| Inclusion/Exclusion Criteria                                           | X                |                           |                           |                                                                                    |                                                                                 |
| Medical History                                                        | X                |                           |                           |                                                                                    |                                                                                 |
| Current Medication                                                     | X                |                           |                           |                                                                                    |                                                                                 |
| Recovery of imaging slides                                             | X                |                           |                           |                                                                                    |                                                                                 |
| Routine Blood Tests a                                       | X                |                           |                           | X                                                                                  |                                                                                 |
| Review of hormonal assessment according to ENSAT criteria b | X                |                           |                           |                                                                                    |                                                                                 |
| Pregnancy Test in women of childbearing potential c         | X                | (X)                       | (X)                       |                                                                                    |                                                                                 |
| Physical Examination, Height, Weight/BSA                               | X                |                           |                           |                                                                                    |                                                                                 |
| Adverse Event / Serious Adverse Event d                     | X                | X                         | X                         | X                                                                                  |                                                                                 |
| 24 hour urine                                                          | X                |                           |                           |                                                                                    |                                                                                 |
| Follow up imaging CT or MRI of adrenal region e             |                  |                           |                           |                                                                                    | (X)                                                                             |
| [  F]Fluorodeoxyglucose PET/CT                            |                  | X (if not at visit 3)     | X (if not at visit 2)     |                                                                                    |                                                                                 |
| [  I]Iodometomidate SPECT/CT                             |                  | X (if not at visit 3)     | X (if not at visit 2)     |                                                                                    |                                                                                 |

- a Routine blood tests: Serum-creatinine, urea, glomerular filtration rate (MDRD), blood count (haemoglobin, leukocytes, platelets), aspartate aminotransferase, alanin aminotransferase, alkaline phosphatase, and gamma glutamyl transferase. If done within 2 weeks before V1, then no need to repeat.
- b Hormonal assessment: Morning serum cortisol after 1 mg dexamethasone 23:00, (urinary free cortisol), (midnight salivary cortisol), baseline plasma ACTH, plasma renin concentration or plasma renin activity, serum aldosterone, (DHEAS), (17-OH-progesterone) , plasma metanephrines/plasma normetanephrines or urinary metanephrine/normetanephrine excretion (*Table 1*)
- c At the discretion of investigator. This should follow usual care at the respective clinic of nuclear medicine, since pregnancy should be ruled out for almost all routine procedures: If in routine care this is only done by questioning then this should suffice.
- d AEs will be collected from inclusion of study to visit 4.
- e Only in case of refusal of surgery, follow up imaging (CT or MRI) will be performed 6-12 months after inclusion into the study and at the discretion of the attending physician

